### Sampling and recruitment process

All patients participating in the program (intervention group) or attending the two clinics (control group) will be screened for eligibility criteria. A list of all eligible participants from each of the three clinics will be compiled every month. Participants will be selected for the study based on computer-generated random numbers until the desired sample size is achieved.

Prior to participation, all participants will be required to provide written informed consent. The consent form will outline the purpose, procedures, benefits, risks, participation requirements, contact information for the Principal Investigator, and information regarding withdrawal from the study. Consent will be collected by a trained member of the research team and stored electronically. Data will be collected at four time points: at the start of the study, at six months, 12, and 18 months after the commencement of the study.

The study period, including the schedule of enrolment, intervention, and assessment of the study groups, is shown in Fig 1.

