### Setting and eligibility criteria

The proposed study will be conducted at the Freedom from Diabetes Clinic, which operates on an online subscription-based model of 1-year duration for the management of diabetes (intervention group). Additionally, the study will include participants from two private clinics in Pune and Ahmedabad (India) (Control Group), which provide standard medical care based on established guidelines for individuals with diabetes. All individuals with T2D who enrol in these centres between March and August 2024 and meet the eligibility criteria will be recruited for this study Table 1.

**Table 1 pone.0306394.t001:** Eligibility criteria for the DiRemI study.

Inclusion Criteria	Exclusion Criteria
Age between 30 and 70 years	Pancreatitis or drug-induced diabetes (Steroids)
Confirmed diagnosis of type 2 diabetes, which may be managed with oral hypoglycemic agents, insulin, Ayurvedic antidiabetic medications, or have an HbA1c level of ≥ 48 mmol/mol (6.5%) with or without medication	Other types of diabetes (type 1 diabetes mellitus, diabetes insipidus, maturity-onset diabetes of the young, latent autoimmune diabetes in adults, or Gestational Diabetes)
Body mass index (BMI) between 25 kg/m^2^ and 35 kg/m^2^	Advanced complications related to nephropathy (eGFR<30 mL/min/1.73 m^2^, urine microalbumin >1000 mg), retinopathy (severe non-proliferative diabetic retinopathy and proliferative diabetic retinopathy), neuropathy (peripheral artery disease or diabetic neuropathy resulting in complete numbness and loss of sensation, amputations, ulcers, foot deformities, Charcot’s foot)
Duration of type 2 diabetes less than 15 years	History of heart attack, cardiac arrhythmia, bypass or stent placement surgery, ischemic heart disease, angina (class II or III), myocardial infarction within the previous 6 months, reported ejection fraction <40%, abnormal ECG, and positive stress test results (moderate or severe)
Ready to provide written informed consent	Known history of cancer
Agree to undergo the examination, lifestyle intervention program, and post-program evaluation	Pregnant and lactating women
Well-oriented in time, space, and as a person	Patients who have required hospitalization for any diabetes-related complications in the last 6 months or for depression or are on antipsychotic drugs

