### Control group (Routine medical care)

The control group will receive routine medical care along with education for management of T2D and its associated comorbidities based on current clinical guidelines.

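### The protocol gives two conflicting entry rules, new enrolment or current attendance, and ties baseline to no comparable starting event in the two groups

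*Protocol article*

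**What the plan says.** Three statements in the protocol article bear on who enters and when follow-up begins.

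- *Setting and eligibility criteria* describes the programme clinic, "which operates on an online subscription-based model of 1-year duration", then the two private clinics that supply controls, and continues: "All individuals with T2D who enrol in these centres between March and August 2024 and meet the eligibility criteria will be recruited for this study". The phrase about centres follows the description of all three, so the enrolment window covers controls as well.
- *Sampling and recruitment process* opens with a different frame: "All patients participating in the program (intervention group) or attending the two clinics (control group) will be screened for eligibility criteria". It then adds: "A list of all eligible participants from each of the three clinics will be compiled every month". Participants are picked from these lists by random numbers.
- The same section places the four assessments "at the start of the study, at six months, 12, and 18 months after the commencement of the study". It does not say whether that start is the first programme day, the first clinic visit or the date of consent.

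On comparator care, *Control group (Routine medical care)* says: "The control group will receive routine medical care along with education for management of T2D and its associated comorbidities based on current clinical guidelines". It does not say whether this care is newly started or continuing. Table 1 has no criterion on being new to a centre.

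**The concern.** Enrolling at a clinic and attending it are different conditions. A patient seen there for years attends but does not enrol in the window. Under the sampling wording such a patient is eligible, and the control baseline is then whichever visit coincided with listing. A programme participant, by contrast, has sought out a time-limited service and may be at its start.

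People who take up a new service may do so when control is poor or motivation is high, and some later improvement could follow under any new care. If one group is richer in new starters than the other, that improvement enters the group difference. Allocation is not randomised, so the design does not balance it. At stake is whether a 12-month difference can be credited to the programme or partly to having just begun something.

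**Working it through.** No figure in the protocol tests this point, so the check is a comparison of the entry rules, followed by an illustration.

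**1. Cross the two rules with the two groups.**

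| Rule applied | Programme group | Control group | Result |
|---|---|---|---|
| Setting section, both groups | enrols March to August 2024 | enrols March to August 2024 | both newly enrolled; no imbalance in newness |
| Sampling section, both groups | anyone on the programme, at its start or partway | anyone attending, for any length of time | time on the programme limited to about one year (barring renewal); time at the clinic unlimited |
| Setting section for programme, sampling section for controls | new starters | any attender | sharpest contrast, but no section states this combination |

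The sections conflict in every case. The imbalance is absent in row 1, possible in row 2 and greatest in row 3.

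**2. Time origin.** The programme is a phased one-year course, and its physician assesses participants at the outset, so programme start is a natural baseline for that group. The text does not name it as such, and names no matching event for controls.

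**3. What could absorb an imbalance.** *Statistical analyses* says adjustment may be considered for baseline level, age, gender and time since diagnosis. Time under current care is not on that list, and time since diagnosis does not stand in for it: someone diagnosed ten years ago may be new to a clinic or settled there. Baseline level would deal partly with entry at a moment of poor control.

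**4. Direction.** *Outcome measures* defines two binary primary outcomes: loss of at least 10% of body weight, and HbA1c under 6.5% held for three months or more off medication.
- New routine care that lowers HbA1c through drugs would not produce remission so defined. An ordinary fresh-start effect therefore does not carry over directly to that outcome.
- A participant listed partway through the programme could have lost weight before baseline, which works against the programme on weight. The same person could already have had medication reduced, which works for it on remission.

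A bias in the programme's favour is plausible, but the documents do not establish it.

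**5. Illustration of scale, on an assumed input.** Inputs from *Sample size determination*: 180 per group, 30% loss, 0.025 per outcome, planned effects d = 0.445 (weight) and 0.635 (HbA1c). Assumed: a shift b of 0.1, 0.2 or 0.3 SD unrelated to the programme, with no true programme effect.

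- Analysed per group: 180 × (1 − 0.30) = 126.
- Standard error of d: √(2/126) = 0.126. Two-sided critical value at 0.025: c = 2.241.
- P(significant) = 1 − Φ(c − b/SE) + Φ(−c − b/SE).

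| Shift b | 126 per group | 180 per group |
|---|---|---|
| 0 | 2.5% | 2.5% |
| 0.1 | 7.5% | 9.9% |
| 0.2 | 25.7% | 36.5% |
| 0.3 | 55.6% | 72.7% |

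A shift of 0.2 is 0.2/0.445 = 45% of the planned weight effect and 0.2/0.635 = 31% of the planned HbA1c effect. These rates apply to a comparison of means, as used for sizing. They are not error rates for the binary primary outcomes.

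**The case against.** A reader might infer that the plan deliberately sets fresh programme starters against settled clinic patients. The documents do not support that. Each section treats the two groups alike: the enrolment window applies to all three centres, and the sampling sentence leaves the programme group as open as the controls. The sharp contrast needs one section for one group and the other section for the other. The sampling sentence can also be read as a monthly screening step inside the March to August window, in which case the problem disappears.

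The illustration is open to objection as well. Its shift is assumed, and it uses means where the outcomes are binary. It shows that a bias of that size would matter, not that one exists.

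Finally, the study is described as matched, the full protocol and analysis plan are not shown, and the timeline figure is missing from the text reviewed. Any of these might fix time zero or account for time under care.

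These objections rule out an unconditional claim of bias. They do not remove the conflict. The screening-step reading is not stated, and the setting section cannot simply be taken to govern: it says every eligible enrolee is recruited, whereas the sampling section draws at random from lists. The sampling section is the operational instruction, and it has the looser wording.

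**Conclusion.** The point holds as a contradiction with a conditional consequence. The article gives two entry rules, and no time origin that means the same thing in both groups. If recruitment follows the sampling section, long-standing controls with an arbitrary baseline may be compared with people at an unspecified point in a one-year subscription. Part of any difference could then reflect starting new care.

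The size is unknown from the documents. The 7.5% to 55.6% range rests wholly on assumed shifts of 0.1 to 0.3 SD and on a comparison of means. A reader might also infer that the bias must favour the programme on both primary outcomes. That is not shown, least of all for drug-free remission, and participants listed mid-programme could pull the two outcomes in different directions.

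The conclusion assumes that the matching scheme and the unseen timeline do not already settle entry and time zero. If the setting section's rule was followed throughout, the imbalance in newness does not arise and only the wording needs correction.

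**What to change.** Amend *Sampling and recruitment process* to agree with *Setting and eligibility criteria*: each month's list, at all three centres, holds only people newly enrolled at that centre in that month. Set baseline for both groups at enrolment, meaning programme start or first clinic visit, and count the 6-, 12- and 18-month assessments from there.

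*Trial status* expected recruitment to run from 1 March to 31 August 2024, so a fallback is needed. If settled attenders or mid-programme participants have already been sampled, record the date of first attendance or of programme start for everyone, and pre-specify an analysis restricted to new enrolees. Restriction is preferable to matching or adjusting on that date, because the groups may barely overlap on it.

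The cost is a short amendment and one date per participant. The monthly control pool shrinks if current attendance was the working rule; it does not change if new enrolment was. The fix does not remove self-selection into a paid programme, which should still be stated as a limitation.

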**Methods:**

The DiRemI study is a prospective, open-label, matched-group trial aimed at assessing the impact of a one-year online integrated intensive lifestyle intervention (ILI) comprising dietary modifications, physical activity, psychological support, and medical management on weight loss and remission in adult T2D patients (aged 30–70 years), with a body mass index (BMI) between 25 and 35 kg/m^2^, and disease duration of <15 years. ILI will be compared with routine medical care (RMC). Participants will be recruited from three clinics: one providing ILI and two others providing RMC. The co-primary outcome will be weight loss and remission at 12 months, with a follow-up at 18 months. The proposed sample size is 360 participants (180 each in intervention and control group).

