## Methods

### Design

The present study is a prospective, open-label, matched control trial. Ethical approval for the study was granted by the Institutional Ethics Committee (IEC) (Ref. no. FFDRF/IEC/2023/3). The trial is prospectively registered with the Clinical Trials Registry-India (CTRI) (Ref. No. CTRI/2023/06/053885) (S1 File). This study will adhere to the standards for clinical research outlined in the Declaration of Helsinki. The protocol is designed according to the SPIRIT guidelines (S1 Checklist).

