### Statistical analyses

Primary outcome measures will be analysed using two-sided statistical tests with a type I error rate of α = 0.05. Primary analysis will be performed using the intention-to-treat method. Categorical data will be compared between the two groups using chi-square or Fisher’s exact tests. Continuous data will be evaluated using parametric or non-parametric tests based on data distribution.

For outliers (± 3 standard deviation), efforts will be made to cross-check and obtain the correct values. Failing this, the case will be considered as missing data. In the case of random missing values, two separate analyses will be performed: one including the cases with missing data by choosing pairwise deletion and the other excluding it using listwise or case-wise deletion. A complete case analysis will be considered if differences are observed between the two analyses. In the case of non-random missing values, the imputation method may be used by replacing the missing value with the mean for that variable.

Potential adjustments for baseline values, age, gender, and disease duration may be considered. Multivariable linear and logistic regression analyses will be used to determine predictors of remission. Finally, subgroup analyses may be performed based on factors such as gender, age, comorbidity, diagnosis length, and severity to investigate potential variations in treatment responses.

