In this context, this study aims to contribute to the growing body of evidence supporting the effectiveness of holistic interventions in managing T2D, particularly in diverse populations, such as those in India. By addressing not only physical health, but also mental well-being and cultural considerations, our findings may pave the way for more tailored and effective diabetes management strategies globally.

Our study has a few limitations that should be considered. First, the socioeconomic status of the participants may limit the generalisability of our findings to the broader Indian context because our online diabetes management program operates on a subscription-based model that may restrict access to those who can afford it. Future trials adopting a randomised-controlled design may be planned based on the outcome of the present study to address this. Second, the study relies on self-reported parameters, such as anthropometry, which may be subject to data errors despite detailed instructions and regular monitoring of incoming data. Additionally, although our study is not a true randomised controlled trial, we have chosen a matched-control group for our intervention group which is more acceptable in a real-world setting. Finally, due to the comprehensive nature of our planned intervention, we will not be able to examine the impact of individual components. Notwithstanding these limitations, we believe that our research will provide valuable insights into the effectiveness of our holistic diabetes management program.

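### The trial is called matched but describes no matching step, and the only committed primary comparison is unadjusted, so baseline differences between the clinics can bias the result

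*Protocol article*

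**What the plan says.** **Label.** The Abstract (Methods) states: "The DiRemI study is a prospective, open-label, matched-group trial". The Design section states: "The present study is a prospective, open-label, matched control trial". The limitations paragraph of the Discussion concedes that the study is not a true randomised trial and answers: "we have chosen a matched-control group for our intervention group which is more acceptable in a real-world setting".

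**Selection.** Under Sampling and recruitment process: "A list of all eligible participants from each of the three clinics will be compiled every month". Then: "Participants will be selected for the study based on computer-generated random numbers until the desired sample size is achieved". Setting and eligibility criteria says something different, namely that all people with type 2 diabetes who enrol at the centres between March and August 2024 and "meet the eligibility criteria will be recruited for this study".

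**Treatment.** The intervention group comes from one clinic that runs a one-year online subscription model. The control group comes from two private clinics giving standard care.

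**Outcomes and analysis.** Both primary outcomes are binary: weight loss of at least 10%, and remission. The Statistical analyses section says: "Categorical data will be compared between the two groups using chi-square" or Fisher's exact tests. On covariates it says: "Potential adjustments for baseline values, age, gender, and disease duration may be considered". Multivariable regression is assigned to finding predictors of remission, not to the comparison of the groups.

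**The concern.** A matched control group is a real safeguard when treatment is not randomised, and the limitations paragraph relies on it. The methods describe a different procedure. Random sampling within a clinic makes the sample represent that clinic, and the expected difference between clinics stays what it was.

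People who buy a year-long intensive programme may differ from patients of an ordinary private clinic in weight, HbA1c, diabetes duration, treatment, education and motivation. The article recognises that the subscription restricts access to those who can afford it, but treats this only as a limit on generalisability. It also bears on the validity of the comparison. If the primary test is unadjusted, the result mixes the effect of the programme with the difference between clinic populations. If adjustment is decided later, in an open-label study, the choice can be made with the results in view.

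**Working it through.** **1. Label against procedure.**

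| Place | What it says |
|---|---|
| Abstract, Design, Discussion | matched |
| Sampling and recruitment process | random-number draw from the clinics' eligible lists |
| Setting and eligibility criteria | all eligible enrolees recruited |
| Anywhere in the article | no matching variable, ratio, caliper or procedure |

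The second and third rows also disagree with each other.

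**2. What controls confounding.** The shared eligibility limits (age 30–70 years, BMI 25–35 kg/m², duration under 15 years, exclusion of advanced complications) narrow some differences. Within those limits the ranges are wide, and treatment may run from no medication to insulin. Optional adjustment could cover baseline values, age, gender and duration. Nothing is committed beyond the eligibility limits.

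**3. Illustration of size.** The plan states no figure on this point, so there is none to reproduce. Inputs:

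- Evaluable per group: 180 × (1 − 0.30) = 126. The 180 and the 30% are from Sample size determination; treating 126 as the number analysed is an assumption.
- True effect: none (assumed).
- Latent shift d = baseline imbalance × correlation with outcome, both assumed: 0.3 × 0.5 = 0.15; 0.5 × 0.5 = 0.25; 0.5 × 0.7 = 0.35.
- Control event rate p₀: 2% to 20% (assumed; the article gives none).

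The intervention group's event rate produced by the imbalance alone is p₁ = 1 − Φ(z − d), where z = Φ⁻¹(1 − p₀). The rejection probability of the uncorrected chi-square test is then the sum of the two binomial probabilities over all tables in which the test rejects. Each cell below gives p₁, then the rejection probability at two-sided 0.05 / 0.025. The first level is in Statistical analyses; the second is the per-outcome level in Sample size determination.

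| p₀ | d = 0.15 | d = 0.25 | d = 0.35 |
|---|---|---|---|
| 2% | 2.9%: 6% / 3% | 3.6%: 10% / 6% | 4.4%: 17% / 11% |
| 5% | 6.8%: 9% / 5% | 8.2%: 17% / 10% | 9.8%: 30% / 21% |
| 10% | 12.9%: 11% / 6% | 15.1%: 23% / 15% | 17.6%: 41% / 31% |
| 20% | 24.5%: 13% / 8% | 27.7%: 30% / 21% | 31.2%: 53% / 42% |

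With d = 0 the test holds its level (4.5% to 5.0% at 0.05), so the excess comes from the imbalance.

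**4. Does adjustment help?** A simulation with a continuous outcome (132 per group, 4,000 runs, no true effect) used one measured covariate differing by 0.3 to 0.5 SD and correlated 0.3 to 0.5 with outcome. The unadjusted comparison had a bias of 0.09 to 0.25 SD and rejected in 12% to 54% of runs. After adjustment for that covariate the bias was near zero and rejection about 5%. This shows the direction only, because the primary outcomes are binary, and it says nothing about unmeasured factors.

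**The case against.** The strongest defence has four parts.

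- **The article is condensed.** A random draw from eligible lists does not exclude a matching constraint, and matching variables may stand in a fuller document. This stands in part: the accurate statement is that no matching is described, and a reader who infers that none took place goes beyond the text. It does not remove the point, because the article does describe its selection step, that step is not matching, and the limitations paragraph relies on the label.
- **Adjustment is named and eligibility is shared.** This is correct. A reader might infer that the plan has no control of confounding at all, and the text does not support that. It supports the narrower claim that the committed test is unadjusted and that adjustment is discretionary.
- **The study does not pose as randomised.** This is also correct. The limitations paragraph says so, and the random numbers select people for the study and do not allocate treatment. There is no ground for saying that the article presents selection as randomisation.
- **The size is assumed.** It is, throughout. A continuous-outcome formula with the same shifts and 126 per group would give 22%, 51% and 79% at 0.05. Those figures do not apply to a chi-square test of binary outcomes and should not be quoted for the primary result.

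**Conclusion.** The concern holds in this form: matching is claimed in three places and described in none, treatment is fixed by clinic, and the only committed comparison of the two primary outcomes is unadjusted. Following the plan as written can give a confounded primary result for both outcomes.

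Under the stated assumptions the false-positive rate at two-sided 0.05 is about 6–13%, 10–30% or 17–53% for shifts of 0.15, 0.25 and 0.35 SD (at 0.025: about 3–8%, 6–21% and 11–42%). The direction and size of the actual baseline differences are unknown, so this shows what is possible and does not predict the bias. The contradiction between label and procedure, and the optional status of adjustment, depend on none of these assumptions.

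**What to change.** 1. **Analysis.** Before outcome data are seen, make a covariate-adjusted comparison primary for both outcomes, for example logistic regression reported as a standardised risk difference, or propensity-score weighting. Fix the covariates now: baseline weight or BMI, HbA1c, diabetes duration, age, sex, education and, where recorded at baseline, glucose-lowering treatment. That last item is not in the article's list of baseline data; the eligibility criteria and the medication outcome only imply it. Report the unadjusted test as secondary.
2. **Label.** Remove the word matched from the Abstract, Design and Discussion. If a matching procedure was in fact used, describe it and analyse accordingly. Matching at selection should not be offered as a simple wording change, because recruitment began on 1 March 2024.
3. **Recruitment.** Reconcile the statement that all eligible enrolees are recruited with the random-number selection.
4. **Interpretation.** State that the effect cannot be separated from clinic, since the intervention is given at one clinic only, or from unmeasured motivation to enrol, and that conclusions are associational.

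The cost is protocol and analysis-plan wording, a little more analysis, and an adjusted estimate that may be less favourable than the crude one.
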